#### Serious adverse events

The research team will report all study-related SAEs to the accredited medical ethics committee within 7 days of first knowledge for SAEs that result in death or life-threatening. All other study-related SAEs will be reported within a period of maximum of 15 days. All study-related SAEs will be followed until a stable situation has been reached and the patients’ GP is contacted or until they have eased.

### Statistical analysis

#### Clinical effectiveness analysis

Clinical effectiveness will be analyzed using two-sided tests with a significance level of P< 0.05. Linear mixed modeling will be used to compare the change in primary and secondary clinical outcome measures over time between both trial arms, based on the intention-to-treat principle (i.e. all data will be included independent of treatment completion). The models will be adjusted for confounders if necessary. If feasible, questionnaires with latent constructs will be analyzed using item response theory (IRT) models. Effectiveness analyses will be performed in IBM SPSS version 26.0 (IBM SPSS Inc., Chicago, IL) and IRT in R, Version 3.5.2. All other descriptive analyses, e.g., concerning non-response, loss to follow-up, comparisons of patient characteristics between intervention and control group, and process evaluation will be analyzed in SPSS version 25 (IBM SPSS Inc., Chicago, IL). To minimize missing data, participants are contacted to participate in all assessments, even if an assessment has been missed.

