### Sample size

Group sample sizes of 64 per trial arm achieve 80,15% power to reject the null hypothesis of equal means, when the population mean difference is 4.0 on the Checklist Individual Strength – subscale Fatigue Severity (CIS-FS) with a standard deviation for both groups of 8.0 and with an alpha of 0.05 (two-sided) [10, 19, 24–26]. Since we expect a dropout after 12 months of 25%, approximately 86 visually impaired patients are required per trial arm (*N* = 172 in total). In a former fatigue study [1], approximately 25% of participants had a paid job and in a previous trial unequal distributions were found in both trial arms [27]. Therefore, randomization will be stratified by employment status as well as by low vision service region represented by a mental healthcare professional to equally distribute numbers of participations per region.

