### Randomization

All patients who provide written informed consent for participation and who meet the inclusion criteria will be individually randomized by the research team. Information on employment status and low vision service region is obtained during the informed consent procedure and baseline assessment. Participants will be allocated to the intervention or control group (Table 2). Randomization will be performed according to a 1:1 ratio using random sequence block randomization (blocks of 2, 4, and 6), taking into account the two stratification parameters. Due to the nature of the intervention participants cannot be masked. Allocation to the intervention or control group will be communicated with the participant by email by an unmasked researcher. At the start of the trial and during telephone contacts, participants are asked not to disclose the nature of their treatment allocation during the follow-up assessments. Masked research assistants will conduct telephone interviews during the follow-up assessments. The research team will regularly check whether a research assistant is still masked by asking to guess to which trial arm a participant is allocated.

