#### Secondary outcomes

Secondary outcomes measure (1) the impact of fatigue on daily life with the Modified Fatigue Impact Scale (MFIS) [34]; (2) adaptation to vision loss and acceptance of the disability in relation to oneself or to others with the 9-item Adaptation to Vision Loss (AVL) [35, 36]; (3) symptoms of depression with the 9-item Patient Health Questionnaire (PHQ-9) [37]; (4) symptoms of anxiety with the Hospital Anxiety Depression scale – Anxiety subscale (HADS-A) [38]; (5) vision-related quality of life with the Impact of Visual Impairment questionnaire (IVI) [39, 40]; (6) work functioning (WRFQ 2.0) [41] and work participation (Work Ability Index 1 item) [42]; (7) perception and assessment of work with the Need for Recovery questionnaire (NFR) [43]; and (8) circadian rhythm sleep disorders, insomnia and hypersomnia with the Holland Sleep Disorders Questionnaire (HSDQ) [44] at baseline, 6, and 12 months. Life events that happened in the past year will be measured at 12 months with the Past Life Events (PLE) questionnaire [45].

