#### Cost-effectiveness and cost-utility analysis

Cost-effectiveness analysis (CEA) and cost-utility analysis (CUA) will be performed from a healthcare and societal perspective. Missing cost and effect data will be imputed using multiple imputation techniques according to the Multivariate Imputation by Chained Equations (MICE) algorithm [54]. The results of the imputed datasets will be pooled using Rubin’s rules [55]. Bias-corrected and accelerated bootstrapping with 5000 replications will be used to calculate 95% confidence intervals around the mean difference in total costs between the two groups for both perspectives. Incremental cost-effectiveness ratios (ICERs) will be computed. Bootstrapping will be used to estimate the uncertainty surrounding the ICERs, which will be plotted graphically on cost-effectiveness planes. Cost-effectiveness acceptability curves will also be estimated. Findings will be integrated with published reports and literature to extrapolate the findings to a national level.

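### Covariate adjustment in the primary model is left to a data-dependent rule that does not commit the two stratification factors or the baseline fatigue score

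*Protocol article*

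**What the plan says.** Under Sample size, the protocol article states that "randomization will be stratified by employment status as well as by low vision service region", and cites unequal arms in a previous trial when explaining the choice. Study design names the same two factors, and Randomization describes blocks of 2, 4 and 6, "taking into account the two stratification parameters".

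Under Clinical effectiveness analysis, a linear mixed model will "compare the change in primary and secondary clinical outcome measures over time between both trial arms", by intention to treat. The only sentence on covariates is "The models will be adjusted for confounders if necessary". It lists no covariates, gives no test of necessity and sets no time by which the choice is made. It neither includes nor excludes the stratification factors, and the form in which baseline CIS-FS enters is not given.

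The sample size is a two-group comparison of means: difference 4.0, SD 8.0, two-sided alpha 0.05, 64 per arm, 80.15% power, raised to 86 per arm (172 in total) for 25% dropout.

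**The concern.** Random allocation leaves no systematic confounding at baseline. Adjustment if necessary can therefore only mean a response to what the data show: a chance imbalance, or a shift in the estimate when a covariate is added. The same section plans a comparison of patient characteristics between arms, which is the natural trigger for such a choice. An analysis plan can add detail to a model, but here the article already states a rule, and the rule is open-ended.

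The rule also fits the design poorly. Employment and region were judged important enough to balance by stratification. Because they will be balanced, a rule that looks for imbalance would tend to leave them out, although a stratified design is the case in which they belong in the model.

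Three things are at stake: room for analyst choice in the primary estimate, a standard error that does not reflect the stratified design, and possibly precision, if change is analysed without using the baseline score efficiently. The administrative table (item 5d) and Randomization give conduct, randomisation and analysis to the same research team, which makes a rule fixed in advance more valuable.

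**Working it through.** **Inputs from the article.** n = 64 per arm, difference 4.0, SD 8.0 (Sample size); entry requires CIS-FS above 35 (Table 1); the scale top is printed as 57 (Primary outcome). On the error rate: "Clinical effectiveness will be analyzed using two-sided tests with a significance level of P< 0.05".

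**Assumed, because not given.** Correlation r between baseline and follow-up, 0.3 to 0.7; baseline SD s0, 4 to 8; share of variance explained by the strata R², 0.05 to 0.10. The 8.0 is taken as the follow-up SD s1; the article does not say whether it refers to scores or to change.

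**1. The plan's own figure.** Two-sample t-test, noncentral t with 126 df: power 80.15%, an exact match. Dropout: 64 / 0.75 = 85.3, so 86 per arm and 172 in total. The normal approximation gives 80.7%; the powers below use that scale.

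**2. Strata left out.** Stratified blocks remove the strata from the true sampling variance, but a model without them keeps that variance in the residual. The standard error is then too large by 1/√(1 − R²), and actual alpha = 2[1 − Φ(1.96/√(1 − R²))].

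| R² (assumed) | SE overstated | Actual alpha | Power, strata omitted | Power, strata included |
|---|---|---|---|---|
| 0.05 | 2.6% | 0.044 | 81.4% | 82.7% |
| 0.10 | 5.4% | 0.039 | 82.0% | 84.6% |

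Power with strata omitted is Φ[(4/1.414 − 1.96)/√(1 − R²)], where 1.414 = 8√(2/64). Power with strata included uses residual SD 8√(1 − R²). The estimate is unbiased either way, and every figure is above the planned power.

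**3. Choosing covariates from the data.** Null simulation, 8,000 runs, 64 per arm, one follow-up, five assumed independent baseline covariates (standardised coefficient 0.4 for one, 0.15 for the other four), nominal alpha 5%:

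- unadjusted: 4.9%; all five covariates: 4.5%
- covariates with imbalance p < 0.10: 3.6%
- covariates that shift the estimate by more than 10%: 4.1%
- smallest p-value of these four analyses: 7.8%

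The simulation standard error for the last figure is √(0.0776 × 0.9224/8000) = 0.3 percentage points. A mechanical selection rule did not inflate the error; free choice among the results did.

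**4. Raw change against baseline adjustment.** Change SD = √(s0² + s1² − 2·r·s0·s1). Baseline-adjusted SD = s1√(1 − r²). The difference in variance is (s0 − r·s1)², which is never negative.

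| s0 | r | Change SD | Adjusted SD | SE ratio | Power, change | Power, adjusted |
|---|---|---|---|---|---|---|
| 8 | 0.3 | 9.47 | 7.63 | 1.24 | 66.7% | 84.3% |
| 8 | 0.5 | 8.00 | 6.93 | 1.15 | 80.7% | 90.4% |
| 8 | 0.7 | 6.20 | 5.71 | 1.085 | 95.5% | 97.7% |
| 5 | 0.3 | 8.06 | 7.63 | 1.06 | 80.1% | 84.3% |
| 5 | 0.5 | 7.00 | 6.93 | 1.01 | 89.8% | 90.4% |
| 4 | 0.5 | 6.93 | 6.93 | 1.00 | 90.4% | 90.4% |

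The first row is an extreme. If the screening score serves as baseline, as the marks in Table 2 suggest, baseline values lie between 36 and 57. A uniform spread over those 22 values has SD √((22² − 1)/12) = 6.3, so a baseline SD of 8 would need scores piled up at both ends.

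**The case against.** The strongest reply is that much of this depends on how a condensed article is read. Comparing change over time in a mixed model is ordinary wording for a repeated-measures model with an arm-by-time term. With baseline means held equal across arms, that model is as efficient as baseline adjustment. How baseline enters is a detail that a full protocol or analysis plan may settle. The strata are not excluded, and omitting them only makes the test conservative. All of this stands. It limits the size of the problem but does not supply a covariate rule.

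A reader might go on to infer three stronger points, which the document does not support:

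- *That the trial is underpowered.* Power of 66.7% needs a raw change-score test, SD 8 at both times and r of 0.3. The article gives none of these, and the entry criterion makes a baseline SD of 8 doubtful. Nor does the article say that the 8.0 is the SD of scores rather than of change.
- *That the 12-month life-events score will be used as a covariate.* The text says only that "Life events that happened in the past year will be measured at 12 months", and nowhere proposes adjusting for it.
- *That the economic comparison is unadjusted.* The article describes bootstrap "95% confidence intervals around the mean difference in total costs between the two groups". It does not say unadjusted, and a bootstrap can be run around a regression.

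**Conclusion.** The point holds as a poorly fixed rule. The adjustment of the primary estimate depends on the observed data, has no criterion, and does not commit the factors by which the trial randomises.

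The size is modest and depends on assumptions. Omitting the strata lowers actual alpha to 0.044 to 0.039 and costs 1.3 to 2.6 points of power, if they explain 5 to 10% of variance. Unrestricted choice among models could bring type I error to about 7.8%; that is a risk of an open rule, not a demonstrated harm. A raw change score would cost between nothing and about 24% in standard error, with the upper end unlikely given the entry criterion. There is no error in the sample size, and no bias follows from leaving out the strata or from analysing change. This is an improvement available at almost no cost, not a fault that threatens the trial.

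**What to change.** Replace the covariate sentence under Clinical effectiveness analysis with: *The primary mixed model will include baseline CIS-FS (as a covariate or with baseline means constrained equal across arms), employment status and low vision service region, fixed before unblinding; any other adjustment uses baseline variables only and is a sensitivity analysis.* Participants know their allocation, so unblinding should be defined here as the first comparison of outcome data by arm.

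Apply the same terms to each secondary clinical outcome, with its own baseline value. Life events, measured only at 12 months, have no baseline value and need none.

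The cost is wording only. The baseline score and both stratification factors are obtained before allocation, so no data collection changes and the sample size stays as it is. The one downside is that sparsely filled regions may have to be merged; the merging rule should rest on counts alone and be fixed at the same time.

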#### Cost-effectiveness and cost-utility analysis

Cost-effectiveness analysis (CEA) and cost-utility analysis (CUA) will be performed from a healthcare and societal perspective. Missing cost and effect data will be imputed using multiple imputation techniques according to the Multivariate Imputation by Chained Equations (MICE) algorithm [54]. The results of the imputed datasets will be pooled using Rubin’s rules [55]. Bias-corrected and accelerated bootstrapping with 5000 replications will be used to calculate 95% confidence intervals around the mean difference in total costs between the two groups for both perspectives. Incremental cost-effectiveness ratios (ICERs) will be computed. Bootstrapping will be used to estimate the uncertainty surrounding the ICERs, which will be plotted graphically on cost-effectiveness planes. Cost-effectiveness acceptability curves will also be estimated. Findings will be integrated with published reports and literature to extrapolate the findings to a national level.

#### Budget impact analysis

Based on the results of the clinical study, the CEA and the CUA, a budget impact analysis (BIA), will be performed to inform decision-makers on the financial consequences of implementing E-nergEYEze into routine practice. Guidelines by the ISPOR Task Force will be used for the BIA, i.e., relevant features of the health care system, access restrictions, anticipated uptake, and the use and effect of current and the new intervention will be taken into account. The BIA will be performed from the healthcare perspective, which includes direct healthcare costs. The study results will be extrapolated, by means of a simple linear model, from a time horizon of 2 years to 5 years, concerning the entire Dutch population. Due to a lack of registration, only an estimated number of people who are visually impaired in the Netherlands can be provided. The extrapolation will assume a constant incidence of fatigue in visually impaired adults. Also, we expect that the detection rate as found in the trial will be stable over time. A factor that is expected to change with time is the uptake of the E-nergEYEze intervention. This factor will be used for scenario analysis in the BIA. For each perspective, we access costs when 10%, 20%, 30%, and 100% of the target group receive E-nergEYEze. These scenarios will be compared with the baseline scenario, reflecting current care, where 0% of the target group is offered E-nergEYEze. Sensitivity analysis will be performed on relevant parameters such as the uptake of E-nergEYEze and unit costs. The source of the unit prices will vary with the perspective. Also, future costs will be indexed and not discounted. The precision of costs will be in accordance with the described perspectives. All analysis will be performed in STATA.

#### Structural equation modeling

Separate path models will be developed to identify the determinants of fatigue severity within a structural equation modeling framework (direct and indirect associations). Mediation will be investigated by inspection of the estimated direct, indirect, and total effects within the path models. Depending on the outcomes of the separate models, each new model will be analyzed by comparing it to the former model using model-fit indices (maximum likelihood estimation), i.e., RMSEA, SRMR, CFI, and TLI. Finally, one structural equation model explaining the working mechanism of the intervention on fatigue will be presented. Analyses will be performed with Mplus version Analyses will be performed with Mplus version 7.4 [55].

### Data management

Patient data will be encrypted by an individual code (from 1000 to 3000), which can be linked to the patient with a separately saved “key file.” Only the research team has access to this key file and it will be deleted after the study has ended. Data will be entered into Castor (data entry software) and converted into the statistical software packages used in this trial. The computer network of Amsterdam University Medical Centers will be used to store all data with a password. The registration forms and signed informed consent forms will be kept in a locked cabinet in a locked room, that is only accessible to the research team. Data will be stored for 15 years, after which it will be destroyed. Minddistrict, the Internet Portal Supplier, will encrypt and securely store all data of patients, i.e. assignments and communication with social workers.

## Discussion

Having vision loss is known to compromise the quality of life and puts people at risk for detrimental health outcomes [3, 4, 36, 56]. Severe fatigue on top of visual impairment is associated with incremental societal costs that largely determine the economic burden of low vision or blindness through loss in work participation and increased healthcare utilization [1]. Currently, there is little evidence that interventions offered within low vision service organizations are beneficial for health- and vision-related quality of life. The proposed intervention contributes to the evidence base of potentially feasible interventions to reduce the important health-related consequences of vision loss [57].

This study is innovative since (1) it focuses on eHealth in people with visual impairment which has only marginally been attempted in previous studies, (2) it focuses on vision-related fatigue which is a significant problem in people with visual impairment for which no evidence-based interventions exist, and (3) it is based on a well-designed RCT.

The blended-care character of E-nergEYEze may be a promising approach for both patient and professional. The intervention has been designed specifically for adults with visual impairment by a group of experts. The tailor-made approach to address specific symptoms of fatigue for visually impaired adults will promote its relevance. E-nergEYEze aims to be accessible, independent of time and place, it stimulates patient empowerment and it may increase treatment capacity by professionals. Taking into account the professionals’ and patients’ perspective, thereby stressing its human-centered design, fits the needs and preferences of all end-users.

The usability and feasibility study will provide insight in the accessibility and feasibility of E-nergEYEze. The RCT will determine if a blended vision-specific eHealth intervention based on cognitive behavioral and self-management leads to a significant reduction of fatigue severity. The pragmatic design of the study allows the intervention to be similar to daily clinical practice, which enhances the generalizability of the results and contributes to its future implementation. These strengths provide opportunities for a cost-effective intervention.

There are possible limitations to mention. First, participants and professionals cannot be masked due to the nature of the study. Results might be overestimated by the intervention group, for example, because a participant who receives E-nergEYEze may be more motivated to positively appraise fatigue symptoms than someone in the control group. This could lead to information bias. Nevertheless, the pragmatic design allows for a good representation of future clinical practice. Second, E-nergEYEze will be available online, for which an internet connection is required. Although it seems counterintuitive, people with a visual impairment frequently use internet applications [58]. Since having access and skills to follow the online intervention are necessary, low vision services will provide intervention-specific assistance at home or at the center to address these needs. Third, the control group will receive care as usual, but the expected effects may have been greater if there was an inactive comparator, such as a control group receiving no care or being on a waiting list. Fourth, the mean difference of 4.0 on the CIS-FS is smaller than the clinical relevant difference of 6.0 in previous studies. This smaller difference was chosen as a mean difference of 6.0 was not achieved after one year in several studies [10, 12, 19, 24]. To accommodate this choice, this study will have a larger sample size. Finally, the follow-up period could be considered short, since the intervention lasts 5 months with a 12-months follow-up from baseline. It would be valuable to determine if expected positive effects of E-nergEYEze are sustained over a longer period of time; however, there is no time or resources to investigate a longer maintenance effect and most of the studies on low vision rehabilitation have a follow-up period of less than 12 months [57].

This intervention has been developed with all important stakeholders of low vision services in the Netherlands to secure a pragmatic design and future implementation success of potentially feasible eHealth interventions. If E-nergEYEze shows that eHealth is an effective treatment for severe fatigue in visually impaired adults, with respect to accessibility and content, the intervention and its results could fulfill the gap in knowledge, skills, and treatment options in low vision services in the Netherlands.

## Trial status

Protocol version number 7, date 04-03-2020. Recruitment began on 6 October 2020 and will be completed in April 2022.

## Data Availability

The datasets analyzed during the current study are available from the corresponding author on reasonable request.

## Abbreviations

CBT: Cognitive behavioral therapy
SM: Self-management
MS: Multiple sclerosis
RCT: Randomized controlled trial
CIS-FS: Checklist Individual Strength – subscale Fatigue Severity
ICT: Information and communication technology
SAE: Serious adverse event
T0: Baseline assessment
MFIS: Modified Fatigue Impact Scale
AVL: Adaptation to Vision Loss
PHQ-9: Patient Health Questionnaire
HADS-A: Hospital Anxiety Depression Scale – subscale Anxiety
IVI: Impact of Visual Impairment
WRFQ: Work Role Functioning Questionnaire
WAS: Work Ability Score
NFR: Need for Recovery
HSDQ: Holland Sleep Disorders Questionnaire
PLE: Past Life Events
EQ-5D-5L: EuroQol-5 Dimensions with 5 Levels
iMCQ: Medical Costs Questionnaire
iPCQ: iMTA Productivity Cost Questionnaire
CCTS-SR: Competencies of Cognitive Therapy Scale – Self Report
MH: Mental Healthcare
BIPQ: Brief Illness Perceptions Questionnaire
SE scale: Self-Efficacy scale
FCS: Fatigue Catastrophizing Scale
IRT: Item Response Theory
CEA: Cost-Effectiveness Analysis
CUA: Cost-Utility Analysis
MICE: Multiple Imputation by Chained Equations
ICERs: Incremental Cost-Effectiveness Ratios
BIA: Budget Impact Analysis
WMO: Medical Research Involving Human Subjects Act
GDPR: EU General Data Protection Regulation
SPIRIT: Standard Protocol Items Recommendations for Interventional Trials
